## Abstract

**Background:**

Continuous feedback on patient improvement and the therapeutic alliance may reduce the number of dropouts and increase patient outcome. There are, however, only three published randomized trials on the effect of feedback on the treatment of eating disorders, showing inconclusive results, and there are no randomized trials on the effect of feedback in group therapy. Accordingly the current randomized clinical trial, initiated in September 2012 at the outpatient clinic for eating disorders at Stolpegaard Psychotherapy Centre, aims to investigate the impact of continuous feedback on attendance and outcome in group psychotherapy.

**Methods/design:**

The hypothesis is that continuous feedback to both patient and therapist on treatment progress and alliance will increase attendance and treatment outcome. The trial is set up using a randomized design with a minimum of 128 patients allocated to either an experimental or control group at a ratio of 1:1. The experimental group will receive standard treatment (systemic and narrative group psychotherapy) with feedback intervention, whereas the control group will receive standard treatment only. The participants are diagnosed with bulimia nervosa, binge eating disorder, or an eating disorder not otherwise specified, according to the DSM-IV. In the experimental group feedback to the participants, based on the Outcome Rating Scale (ORS) and the Group Session Rating Scale (GSRS), is actively added to standard treatment. The ORS assesses areas of life functioning known to change as a result of therapeutic intervention. The GSRS assesses key dimensions of effective therapeutic relationships. In the control group, the patients fill out the Outcome Rating Scale only, and feedback is not provided.

The primary outcome is the rate of attendance to treatment sessions. The secondary outcome is the severity of eating disorder symptoms. Exploratory outcomes are the level of psychological and social functioning, and suicide or self-harm. This is measured with the ORS, Symptom Check List, WHO-Five Wellbeing Index, Sheehan Disability Scale and a modified version of the Self-Harm Inventory.

**Discussion:**

If the results will confirm the hypothesis, this trial will support feedback as a way to improve group treatment attendance for outpatients with eating disorders.

**Trial registration:**

ClinicalTrials.gov identifier: NCT01693237

## Background

Eating disorders are serious mental disorders affecting up to 10% of the population, primarily women [1,2]. Characteristics of eating disorders are severe disturbances in eating behaviour [3] with significant physical, psychological and social consequences for the individual and his or her relatives. According to the DSM-IV, there are two specific diagnoses: anorexia nervosa (AN) and bulimia nervosa (BN). Disorders that do not meet the criteria for a specific eating disorder are classified as eating disorders not otherwise specified (EDNOS) [3]. However a third diagnosis, binge eating disorder (BED), is included in the appendix of the DSM-IV as a ‘diagnosis for further study’. We are diagnosing BED according to the research criteria defined in DSM-IV. In the fifth version of the DSM, BED is recognized as a free-standing diagnosis [4].

### Dropout and non-attendance in psychotherapy

The term ‘dropout’ refers to patients that choose to end treatment prematurely. It is a common phenomenon in psychotherapy. A recent comprehensive meta-analysis, analyzing 669 studies and 83,834 adult patients with a non-psychotic disorder, reported that, on average, 19.7% of patients dropped out of psychotherapy. The dropout proportion for a subsample of patients with eating disorders was even higher at 23.9% [5].

Previous research has indicated that patients who discontinue treatment prematurely exhibit poorer treatment outcomes [5,6]. In group therapy especially, dropout not only affects the patients themselves and their therapists, but can also have an adverse effect on the remaining group members, sometimes resulting in a ‘wave effect’ with dropouts begetting other dropouts [6].

Related to dropout is the phenomenon of irregular attendance to treatment sessions. It has been demonstrated that psychotherapy attendance is associated with the outcome of treatment [7-9] and, accordingly, the development and testing of interventions to increase attendance and prevent dropout from psychotherapy is highly relevant.

### Feedback-informed psychotherapy

One of the ways to specifically address non-attendance and dropout in psychotherapy is by monitoring patient progress. Since 1996, when Howard *et al.*[10] published their session-to-session measures of client progress, there has been an increasing interest in this method and there are now several outcome monitoring systems available [11-13].

Most of the effectiveness research of feedback-informed psychotherapy is based on the Outcome Questionnaire System (OQ System) [11,12,14,15] and the Partners for Change Outcome Management System: International Center for Clinical Excellence (PCOMS ICCE) [12,16-18]. Both systems are based on a patient-focused perspective, where the patient’s goals, ideas for change, and perceptions of the therapeutic alliance are a focus rather than the specific treatment [16,19].

In the remainder of this paper, we will refer to PCOMS ICCE as ‘feedback-informed treatment’ (FIT)*.* FIT is defined as ‘a pantheoretical approach for evaluating and improving the quality and effectiveness of behavioral health services’ [18]. By filling out the measures, the patient continuously evaluates the therapeutic alliance and outcome. This feedback allows the therapist to monitor the progress from session to session and to tailor the treatment in dialogue with the patient. FIT consists of the Outcome Rating Scale (ORS), the Session Rating Scale (SRS) and the Group Session Rating Scale (GSRS) [17]. Information about FIT and intervention strategies are accessible in six different manuals [20]. In January 2013, FIT was recognized as an evidence-based practice by the National Registry of Evidence-based Programs and Practices [21].

### Previous research on the use of feedback in psychotherapy of eating disorders

Results from previous meta-analyses have indicated that feedback has a significant positive effect on psychotherapy outcome [11,22,23]. However, none of these reviews have reported results for subgroups of patients with eating disorders. We therefore searched PsycInfo, PubMed, Embase and the Cochrane Library on 1 October 2013 with the search terms eating disorder*, bulimi* nervosa, anorexi* nervosa, binge eating disorder*, EDNOS and feedback, routine outcome monitoring, and tracking. From the search, we identified three randomized trials [24-26] which we will review in the following.

Schmidt *et al.*[24] included 61 women with BN or EDNOS. They were randomly allocated to 14 sessions of cognitive behavioral guided self-care with or without added personalized feedback. The authors found no effect of feedback on treatment dropout (*P* = 0.672) but it had a significant effect on dietary restriction (*P =* 0.03).

Truitt *et al.*[26] included 51 women with AN or BN and randomly assigned them to treatment with or without feedback. In this trial, the feedback (therapists received feedback, patients did not) significantly predicted change in individual global psychological dysfunction (measured with the OQ System) across the course of treatment (*P* = 0.017).

Simon *et al.*[25] included 133 women diagnosed with AN, BN or EDNOS in their trial. Patients were randomly assigned to treatment with or without feedback using a randomized block design, with therapists serving as the blocking variable (the same therapists provided both treatments). The patients used the OQ System, which, together with Body Mass Index (BMI), was used as an outcome measure. The difference between the feedback condition and no feedback condition at end of treatment was statistically significant and showed an effect size difference of Cohen’s *d* = 0.30. The feedback did not have a significant effect on BMI, which was against the researchers’ initial expectations.

The results in the Schmidt *et al.* and Truitt *et al.* trials [24,26] were challenged by small sample sizes (N = 61 and N = 51), which limits the generalizability and increases the risk of random errors. In the Truitt *et al.* trial [26], the treatment intervention was not described in the dissertation, which makes the trial impossible to repeat. The feedback method in the Schmidt *et al.* trial [24] was defined as ‘personalized feedback on current physical and psychological status, risk and problems, and variables facilitating or hindering change’. The feedback differs from the OQ System and FIT in frequency (not used regularly during therapy) and seems to focus primarily on symptom status rather than on the therapeutic process. These differences reduce the external validity of the findings. The different outcome measures used in the trials can yield different results: Schmidt *et al.* only reported eating disorders symptoms; Truitt *et al.* reported psychological dysfunction in more broad terms (including the OQ score); and Simon *et al.* used the OQ score and BMI as outcome measures.

Previous research has indicated that feedback has a promising effect on maximizing the benefits of psychotherapy. Because only three of the identified trials (with different designs, feedback measures and/or timing and outcome measures) included patients with eating disorders [18,19,21], the benefits of feedback are still inconclusive for these patients. Furthermore, none of the trials were performed in a group therapy setting. 

### Objective

The trial’s objective is to examine the benefits and harms of continuous feedback on treatment progress and alliance in group therapy to patients and therapists. We hypothesize that continuous feedback with subsequent adjustments of the treatment, will increase treatment attendance and treatment outcome.

## Methods/design

The current trial is an investigator-initiated, randomized clinical superiority trial. The experimental intervention is the addition of feedback to standard treatment, and the design strategy can thus be categorized as additive or constructive [27].

After the patients have been offered treatment, received information about the trial, and signed the consent form, the patients are allocated to one of two groups (at a ratio of 1:1). The first (experimental) group consists of standard treatment with feedback intervention (feedback: ORS and GSRS are filled out and included in the treatment according to the FIT intervention manual). The second (control) group consists of standard treatment without feedback intervention (no feedback: ORS is filled out but not included in the treatment).

### Participants

#### **
*Selection and withdrawal of participants*
**

The inclusion and exclusion criteria are divided into criteria that are part of the clinical routine at the trial site, and criteria that are exclusive to the trial (Table 1). Patients excluded as part of the clinical routine will be referred to treatment elsewhere or back to the referring professional. Patients that are offered treatment but are not eligible for inclusion in the trial will receive standard treatment. Excluded patients can be reassessed and included in the trial at a later point in time, if, for example, they have been successfully treated for severe depression and subsequently fulfil the inclusion criteria.

**Table 1 T1:** Inclusion and exclusion criteria

	**Clinical routine**	**Trial specific**
**Inclusion criteria**	• Aged 18 or older	• BN, BED or EDNOS is the primary diagnosis
	• Body Mass Index (BMI = kg/m^2^) ≥ 20	• Diagnosis according to the DSM-IV
		• Written informed consent
**Exclusion criteria**	• Acute suicidal risk	• Severe or non-regulated physical co-morbidity
	• Psychosis	
	• Severe depression	• Pregnancy
	• Abuse of alcohol, medicine and/or narcotics up to 3 months before referral	• Unable to understand Danish
		• Previous participation in the current trial
	• Use of cannabis once a month is accepted at intake but must stop during treatment	• Considered unable to attend treatment sessions as planned
		• Lack of informed consent
	• Concomitant psychotherapeutic/psychiatric treatment outside Stolpegaard Psychotherapy Centre	

BED, binge eating disorder; BMI, Body Mass Index; BN, bulimia nervosa; EDNOS, eating disorder not otherwise specified.

### Participant withdrawal

Participation in the trial is voluntary and patients can withdraw from the trial at any time, without any implications for current or future treatment at Stolpegaard Psychotherapy Centre. The participants are kindly asked to specify which aspects of the trial they wish to withdraw from: the intervention, participation in follow-up assessments, or complete withdrawal from the trial. The options are described in the written patient information.

### Informed consent

Information about participation in the trial will be given at three different points before the patients start therapy: 1) written information before the first routine assessment interview; 2) verbal information at a routine assessment with a psychiatrist or an attending physician; and 3) verbal information at an assessment session with the principal investigator or a qualified assistant. The participants can give their written consent at any point before randomization.

### Therapists

Fifteen therapists are participating in the trial, three male and twelve female (mean age = 44.3 years, SD 9.1). Their general average experience with psychotherapy is 7.2 years (SD 6.6), and their average experience with the treatment of eating disorders is 3.8 years (SD 5.2).

As part of the clinical routine, the therapists have case supervision in groups with team colleagues every other week, lasting one and a half hours. The supervision format is systemic and narrative, structured around the idea of ‘reflecting teams’ [28].

Before data collection began, the therapists had two training sessions (three hours each) in feedback-informed clinical work, led by an external certified FIT trainer and associate at the International Center for Clinical Excellence [20]. The therapists were introduced to the method and instructed in the use of the measures in clinical practice [17]. Only two had worked with FIT in previous jobs. Each therapist was placed in both a control group and an experimental group and thus provided both treatments. To ensure that the therapists followed the feedback method and to reinforce the implementation process, the training was supplemented with one and a half hour hour monthly FIT supervision during the data collection period.

The therapists were assumed to be following the feedback method adequately after this, with no further control for adherence to the method. Because of the lack of published guidelines for the use of feedback in group therapy, the therapists were encouraged to use the feedback according to the guidelines for individual therapy [17]. In cases where these guidelines were insufficient, the supervisor was involved.

Immediately after the second training session with the FIT trainer, the therapists answered an attitude survey ([name]; allegiance measure; unpublished data) asking if they believed working with GSRS and ORS would make a positive difference in their therapeutic work. All therapists agreed that it would improve their clinical work. This therapist allegiance can potentially positively influence the results and exaggerate an effect of feedback on outcome. In order to investigate if the first attitude survey was influenced by the ‘rush’ after the training session, we asked the therapists again before they started using the method. The answers were the same in the second survey ([name]; allegiance measure; unpublished data).

### Standard treatment

Standard treatment is offered in both groups, based on recommendations from the Danish National Board of Health [2] and on guidelines for treating eating disorders in the Capital Region of Denmark [29]. After the initial assessment interview a psychiatrist or attending physician decides to offer the patient one of two standard treatments: basic or elaborate. This decision is based upon an assessment of eating disorder severity, co-morbidity, and medical and/or social factors that are believed to complicate the treatment of the eating disorder.

Treatment length (from the first assessment session to the last follow-up session) is approximately 10 months for basic treatment and 12 to 14 months for elaborate treatment [29]. After referral and before starting group therapy, the patient undergoes a psychiatric, medical, and somatic assessment, followed by psycho-education. The treatment program consists of 20 sessions for patients with BN or EDNOS, and 25 sessions for patients with BED. Alongside group therapy, the patients are offered sessions with a dietician and relatives as well as sessions with a social worker (as needed). The patients in the elaborate treatment are offered an extended medical assessment and more sessions with relatives and a dietician. In some cases, patients start psychotropic drugs before or during treatment; this is a possibility in both groups. Patient treatment status is assessed at weekly team conferences.

### Therapeutic approach and elements

The eating disorders treatment provided at Stolpegaard Psychotherapy Centre is founded on systemic and narrative theory and a post-modern view on patients and therapy [30-33]. The therapists work with individual therapy in the group, which is structured around the principles of the reflecting team [28]. One of the methods used in the therapy is externalization of the eating disorder [30]. With a focus on the patients’ resources, relations, future and unique outcomes [34], patients and therapists address psychological, physiological and social difficulties associated with the eating disorder. The effectiveness of this specific treatment has not been evaluated but a recent meta-analysis of 38 randomized controlled trials showed that systemic therapy, on which the treatment at the Stolpegaard Psychotherapy Centre outpatient clinic is based, is an effective psychotherapeutic treatment for adults with eating disorders and other psychiatric disorders [35].

### Structure

There are seven patients and two therapists in each group. The groups are slow-open, that is, open to new patients as others end treatment. Central to the treatment is a food diary that patients are asked to keep and discuss in the group therapy sessions. Patients are weighed before each session and weight fluctuation is monitored and addressed in the case of rapid weight gain or weight loss. The patients are encouraged to set individual goals for the treatment, typically concerning food, body and appearance, relations, and future [36]. The duration of a group session is 150 minutes.

### Experimental group (feedback)

In the experimental group two sets of measures are added to the standard treatment: ORS and GSRS.

The patients mark their scores on the ORS and GSRS using a tablet computer with a computer-based application (FIT-Outcomes). FIT-Outcomes (FIT-Outcomes, Hoersholm, Denmark) is an application used to administer, score and aggregate data from the ORS and SRS/GSRS [37]. When the patient has marked his or her scores on the tablet computer, the management system produces a graph illustrating the therapeutic progress on the ORS and GSRS, the cutoff scores and the expected treatment response (ETR). Based on the latest score on the ORS and GSRS, FIT-Outcomes provides immediate feedback to the therapists. The therapists discuss the ORS and GSRS score with the patient in the present or the following group session [17].

### The outcome rating scale (ORS)

Before they are weighed and immediately before each group session, the patients complete the ORS and assess their individual, interpersonal, social, and overall wellbeing during the preceding week. The clinical cutoff score is 25 and the reliable change index (RCI) is 5 points [17]. A green alert in the FIT-Outcomes system means that the patient is on track, that is, that the latest score indicates progress similar to successful treatment courses. A red alert means that the patient is off track, that is, that the latest score indicates progress similar to unsuccessful treatment courses. A yellow alert means an uncertain tendency (that the change is smaller than expected). The therapists are encouraged to discuss yellow and red feedback with the patients as soon as possible [17].

### The group session rating scale

The patients mark a score on the GSRS 5 to 10 minutes before the group session ends, and the therapists respond briefly to the score. On the GSRS, the patients rate the present group session concerning relationship*,* goals and topics*,* approach or method and overall. The clinical cutoff score is 36. As described for the ORS, a green alert from FIT-Outcomes means that there is no reason for an intervention. A red alert encourages the therapists to consider alliance feedback, either due to a below cutoff score or a drop on the GSRS of more than one point. The therapists are encouraged to discuss red feedback in the present or following group session.

### Standard treatment (no feedback)

In the control group*,* the patients fill out a paper version of the ORS before each group session. However, they will not receive any feedback during therapy. The ORS forms are gathered in sealed envelopes and put away until data analyses.

### Outcomes

The primary outcome is treatment attendance in the intervention period, defined as a rate (number of attended therapy sessions divided by the number of planned therapy sessions). If a patient ends therapy prematurely, and this is in accordance with the therapists, the number of attended sessions will be set equal to the planned number of sessions. The secondary outcome is the global score of eating disorder examination (EDE) interview, assessed at the end of intervention. The mean score in the two intervention groups are compared.

The exploratory outcomes are: ORS, the Symptom Check List (SCL-90R), the Sheehan Disability Scale (SDS), the WHO-Five Wellbeing Index (WHO-5), and suicide and self-harm.

For all outcomes except the ORS, the scores obtained in the two intervention groups after the end of the treatment are compared. With regard to the ORS, the last available score for each patient in the two groups is compared (see further description of these outcomes below).

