### Outcomes

The primary outcome is the rate of attendance. It is defined as the number of group sessions the patient has attended over the number of planned sessions (20 or 25 sessions). If at group session # n (n <20) the therapist decides that the patient needs not attend further sessions, the number of planned sessions is set equal to n. When a patient discontinues treatment early, the therapists decide whether this is in accordance with the treatment plan (categorized as ‘planned withdrawal’ or ‘unplanned withdrawal’).

In the analysis of the rate data, the model fit of a Poisson model and a negative binomial model both with offset equal to log (number of planned sessions) are compared and the best fitting model is chosen provided it fits the data reasonably well. In the analysis of continuous outcomes the univariate general linear model is used. If the assumptions of a regression are not fulfilled, a non-parametric test is used (Mann-Whitney).

All outcomes are analyzed using regression analyses, including the binary intervention indicator. The primary results are those adjusted by the protocol-specified stratification variables and (where measured) the baseline value as covariates. In an exploratory analysis the analyses will be repeated with the categorical variable ID-group (identity code of the group) as an additional covariate, and it will be tested if the outcome depends on the treatment group. Then it will be tested if ID-group and the intervention indicator interact. If so, subgroup analyses of the various treatment groups will be conducted.

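### The early-ending credit in the attendance outcome depends on therapist agreement, not on the reason, so an agreed ending for worsening or transfer can be scored as full attendance

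*Protocol article*

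**What the plan says.** The Protocol article defines the primary outcome twice.

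- **Methods/design, Outcomes.** The outcome is a rate of attended over planned sessions. For early endings: "If a patient ends therapy prematurely, and this is in accordance with the therapists, the number of attended sessions will be set equal"; the planned count is substituted. The numerator is raised, so the rate is 1.00. No reason for ending is required.
- **Statistical analysis plan, Outcomes.** If, at session n below 20, "the therapist decides that the patient needs not attend further sessions, the number of planned sessions is set equal to n". Here the denominator is lowered, so the rate is attended/n. For early discontinuation, "the therapists decide whether this is in accordance with the treatment plan", with two labels: planned or unplanned withdrawal.

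Under Randomization and blinding, therapists know the allocation. A blinded assessor counts attendance and checks the medical file. The section gives therapists' assessment of withdrawal as an example of the bias this is meant to prevent.

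Table 1 lists acute suicidal risk, psychosis, severe depression and substance abuse as clinic-routine exclusions, and states: "Patients excluded as part of the clinical routine will be referred to treatment elsewhere or back to the referring professional". These are intake criteria. The article does not say how an early ending is scored if such a condition arises during therapy.

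**The concern.** The category that earns the credit joins two opposite courses. One patient stops because no more sessions are needed. Another stops, with the therapists' agreement, because the patient is doing badly and goes elsewhere. Under the Methods rule both score 1.00. The planned/unplanned split does not separate them, because an agreed transfer can be called planned. The blinded assessor protects the count, but cannot separate courses that the definition merges.

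Two things are at stake. First, the rate is hard to interpret: part of it may reflect sessions not attended by patients who did poorly. Second, the judgement that triggers the credit is made by people who know the allocation, so unequal use of it between arms would shift the treatment comparison. Under Multiplicity, the eating disorder examination (EDE) score is tested only if attendance is significant, so a shifted primary result would also decide whether that test takes place.

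**Working it through.** **Inputs.** Planned sessions 20 (BN, EDNOS) or 25 (BED), from Standard treatment. From Sample size estimation: target difference 3 sessions, SD 6, 64 per arm at 80% power or 85 per arm at 90%, and routine mean attendance 13.58 sessions. Two-sided 5%, from Statistical analysis plan. The number and timing of agreed endings for worsening or transfer are not given; every count below is an assumption.

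**The plan's own figure.** With difference 3, SD 6 and two-sided 5%, the t test gives 80.1% power at 64 per arm and 90.0% at 85 per arm. The stated 128 and 170 reproduce. The calculation is in attended sessions and mentions no credit.

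**Scoring one agreed early leaver (20 planned).**

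| Ends at session | Attended | Methods rule | Analysis-section rule (attended/n) | No credit (attended/20) |
|---|---|---|---|---|
| 6 | 5 | 1.00 | 0.83 | 0.25 |
| 10 | 8 | 1.00 | 0.80 | 0.40 |
| 15 | 12 | 1.00 | 0.80 | 0.60 |

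The two sections give different values for the same patient whenever a session up to n was missed.

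**Shift in an arm's mean under the Methods rule.** With an excess of k such endings at session n, all n sessions attended, in an arm of 64:

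shift = k × (20 − n) / 64

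- k = 5, n = 8: 5 × 12 / 64 = 0.94 sessions, which is 31% of 3. On the rate scale, 5 × 0.60 / 64 = 0.047.
- k = 3, n = 12: 3 × 8 / 64 = 0.38 sessions (13%).
- k = 8, n = 4: 8 × 16 / 64 = 2.0 sessions (67%). This needs an excess of 8/64 = 12.5 percentage points, all very early, so it is an upper case.

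**The same case under the analysis-section rule.** The planned model has an offset of log(planned sessions), so the pooled rate is what matters. Assume that the other 59 patients attend 13.58 of 20, and that 5 end at session 8 with all 8 attended.

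- No credit: (59 × 13.58 + 5 × 8) / (64 × 20) = 841.22 / 1280 = 0.657.
- Analysis-section rule: 841.22 / (59 × 20 + 5 × 8) = 841.22 / 1220 = 0.690.
- Difference 0.032, against 0.047 under the Methods rule: about a third smaller. If these patients had also missed sessions before n, each would score below 1.00.

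**The case against.** A reader might infer that patients moved out for worsening or suicidal risk are scored as perfect attenders, that this happens more often under feedback, and that harm therefore counts as benefit. The documents do not support that.

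- No section says that such transfers are credited. The Table 1 conditions are checked at intake, and the analysis-section wording points most naturally to need met. An emergency transfer fits neither label comfortably.
- An automatic 1.00 follows from the Methods rule alone.
- More such endings under feedback is conjecture. Only feedback therapists see the alerts ("A red alert means that the patient is off track"), but these prompt discussion with the patient, and nothing links them to transfer. Weekly team conferences review patients' status, therapists work in both arms, and feedback could equally prevent deterioration. If the arms use the credit equally, both rates rise.
- Harm is also measured separately, by the blinded EDE, the symptom and functioning scales, and the self-harm questions.

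All of this stands, and it limits the claim to what the rule permits. It is also fair that scoring a clinician-directed transfer is partly an estimand choice: the Background describes dropout as the patient's own choice to end treatment, and one may reasonably not count a directed ending against attendance. It does not follow that the ending should count as full attendance, or that two incompatible formulas can stand. The separate harm outcomes do not correct the value that the primary outcome takes.

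**Conclusion.** The point holds as a defect in how a stated primary-outcome rule is fixed. The Methods rule gives full attendance for any agreed early ending, whatever the reason. The analysis section uses a different formula and likewise has no criterion that separates success from worsening. Unblinded therapists decide, so an imbalance in such endings would bias the comparison in either direction.

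The size cannot be known from the documents. Under the Methods rule, assumed excesses of 3 to 8 endings in an arm of 64 shift the mean by 0.38 to 2.0 sessions against a target of 3, with 0.94 (31%) for the middle case. In that middle case the analysis-section rule gives about a third less on the rate scale. These figures assume that all sessions up to the ending were attended and that 20 were planned. They show what the rule allows; they do not predict what will happen. The change is worth making because it is cheap and concerns the primary outcome. The sample size is not in question.

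**What to change.** 1. Reconcile the two Outcomes sections into one scoring rule, and let it cover the 25-session programme: the present n below 20 condition leaves out BED patients who end at sessions 20 to 24.
2. Give the early-ending credit only when the recorded reason is that treatment was completed or its goals reached, as read from the medical file by the blinded assessor.
3. Score all other early endings as sessions attended over the 20 or 25 originally planned.
4. Add a sensitivity analysis of attended over originally planned sessions, with no credit for anyone.
5. Report early endings by reason and arm.

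The cost is a sentence or two in the outcome definition, one reason code beside the existing planned/unplanned label, and one further run of the model. The assessor already checks the file. Attendance rates become slightly lower in both arms, and clinician-directed transfers count as non-attendance; showing the credited and uncredited analyses together makes the effect of that choice visible. The change concerns scoring only, not when or why a patient should leave the group.
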